### Outcomes and Measurement

The primary outcome (on which sample size calculations are based) is the change in HbA_1c _between baseline and the 18 month follow-up visit. Patient-reported rates of severe hypoglycaemia (defined as a hypoglycaemic episode requiring the assistance of another person for treatment) will be reported as a secondary outcome along with change in weight and in psychosocial measures of wellbeing and quality of life.

Table 2 shows the measurement plan for the study. Because of the potential for inter-laboratory variation in the method and reporting of HbA_1c _results this outcome variable was assayed centrally. Blood was sent to the Royal Victoria Hospital in Belfast which has a track record of co-ordinating laboratory measurements for large scale studies. The method used was a DCCT-aligned HPLC assay (ADAMS-A_1c _HA-8160). Lipid levels were measured in the local laboratory in each hospital. License agreements were obtained for all questionnaires used in the study. The **Diabetes-Specific Quality of Life Scale (DSQOLS) **was originally developed in Germany [20] and is a quality of life measure specific for people with type 1 diabetes. It consists of 10 goal or preference items that are weighted to 10 satisfaction items resulting in a preference-weighted treatment satisfaction score. A further 57 items form 8 domains and are rated on a 6-point Likert scale with a total score reflecting quality of life. The domains are social relations, leisure time flexibility, physical complaints, worries about the future, diet restrictions, daily hassles, fear of hypoglycaemia and daily burdens & restrictions. For use in the Irish DAFNE Study the scale was altered slightly from the original to reflect linguistic differences and more culturally appropriate scale-items. These slight modifications did not alter the psychometric properties of the instrument [21]. The **Problem Areas in Diabetes (PAID) **measure is a 20 item questionnaire that uses a Likert-scale to assess an individual's diabetes-related distress [22]. The **Hospital Anxiety and Depression Scale (HADS) **is a dual instrument that uses 7 items along a Likert-scale to measure both anxiety and depression [23]. It is a suitable self-rating scale for anxiety and depression in patients with both somatic and diagnosed mental health issues with good reliability and responsiveness [24].

**Table 2 T2:** Data collections and follow-up intervals

	**Baseline**	**6 month**	**12 month**	**18 month**
**Weight**	x	x	x	x

**Central HbA**_**1c**_	x	x	x	x

**Lipid panel**	x	x	x	x

**QOL measures (DSQOLS, EQ-5D, PAID, HADS)**	x	x	x	x

**Rate of severe hypoglycaemia**	x	x	x	x

DSQOLS - Diabetes-Specific Quality of Life Scale; PAID - Problem Areas in Diabetes; HADS - Hospital Anxiety and Depression Scale

The Irish DAFNE Study also includes a qualitative sub-study and a health economic analysis. The qualitative research involves in-depth interviews of a sub-set of participants at 6 weeks, 6 months and 12 months after delivery of the DAFNE course. The aim of this work is to explore participants' attitudes towards DAFNE and the different methods of follow-up being evaluated in the main study. The health economic analysis will identify, measure, value and compare the costs and outcomes of the 2 different methods of follow-up of DAFNE graduates and examine both of these relative to usual care. A health economic questionnaire has been developed specifically for the study and this is administered at baseline and at 6, 12 and 18 months following DAFNE training.

### Statistical Considerations

#### Sample Size

We used a sample size calculator designed for cluster randomised trials [25]. We based the sample size calculation on an anticipated HbA_1c _difference between the 2 arms of the study of 0.5 percent from month 6 onwards. This came from the observation in the UK study that DAFNE training led to a 1.0 percent drop in HbA_1c _at 6 months but reverted to 0.5 percent by 12 months [9]. Our study hypothesis is that group follow-up will be able to maintain the benefit out to 18 months. Unlike the UK DAFNE Study patients were not excluded with baseline HbA_1c _below 7.5 percent. Based on a standard deviation of HbA_1c _of 1.2 and an intra-class correlation co-efficient of 0.05 we estimated that 450 patients would be required to detect a 0.5 percent difference with 90 percent power.

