### Randomisation and Patient Recruitment

In the study we used a cluster randomisation with the unit of randomisation being the participating DAFNE centre. There are 6 participating centres in this study and it was anticipated that each cluster would have approximately 75 participants each. We felt that DAFNE educators would not be able to separate the 2 approaches to follow-up if they were expected to deliver both. By randomising centres to deliver one or other method of follow-up we hoped to minimise or avoid contamination between the two arms of the study. The process of randomisation of centres was undertaken by a statistician not involved in the study and who was blind to the identity of the hospitals being randomised. The randomisation was done using a computer-generated table of random numbers.

Prior to the study each of the participating DAFNE centres used a similar approach to filling DAFNE courses. A waiting list was maintained of individuals with Type 1 diabetes attending the centre who had expressed an interest in receiving DAFNE training. Using this list, groups of approximately 50 patients were invited to attend a recruitment evening in which the DAFNE course was described and members of the DAFNE team were available to answer questions. A brief description of the study aims and objectives was included in the material presented at the recruitment evening. Individuals were asked to consider participating in the study but were not required to give an answer at the recruitment evening. Following the recruitment evening approximately 6 DAFNE courses (each comprising 8 participants) would be filled. Prior to the week of DAFNE training, individuals were invited to attend a pre-course assessment visit. During this visit a DAFNE educator would make sure that the individual met the inclusion criteria for the study. Informed consent was generally obtained at this visit and baseline study questionnaires were given to the patient.

Study Inclusion criteria:

1. At least 18 years of age at recruitment

2. Diagnosed with type 1 diabetes for at least one year

3. Attending the adult diabetes clinic in one of the participating centres

4. The ability to speak and read English

5. A willingness to monitor blood sugar levels at regular intervals

6. A willingness to transition to a basal/bolus insulin regimen prior to DAFNE training (if not already on such a regimen)

7. A glycosylated haemoglobin (HbA_1c_) level below 13 percent at recruitment.

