#### Sub-group analyses

For those individuals with HbA_1c _above and below 7.5 percent at baseline a separate intention-to-treat analysis will be conducted to compare differences between HbA_1c _at baseline and at 18 months in the 2 treatment arms. Changes in the rate of severe hypoglycaemia will also be examined for those with baseline HbA_1c _above and below 7.5 percent at baseline. The rationale for this approach is that "benefit" from DAFNE training for individuals with low HbA_1c _may amount to a reduction in the frequency of severe hypoglycaemia.

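### The stated 90% power for 450 patients does not follow from the printed inputs: with 6 centres of about 75, SD 1.2 and ICC 0.05, power is about 53% (normal approximation) at an assumed two-sided alpha of 0.05

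*Protocol article*

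**What the plan says.** The Sample Size section reports that a calculator for cluster randomised trials was used. Its target is a "difference between the 2 arms of the study of 0.5 percent from month 6 onwards". The variability inputs are a standard deviation of HbA1c "of 1.2 and an intra-class correlation co-efficient of 0.05". The result is given as: "we estimated that 450 patients would be required to detect a 0.5 percent difference with 90 percent power".

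Randomisation and Patient Recruitment describes "cluster randomisation with the unit of randomisation being the participating DAFNE centre", and adds: "There are 6 participating centres in this study and it was anticipated that each cluster would have approximately 75 participants each". Six centres of 75 make exactly 450. DAFNE and Study Interventions refers to 3 intervention arm centres, so the allocation is 3 to 3.

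Outcomes and Measurement makes the change in HbA1c from baseline to 18 months the primary outcome and says that the sample size rests on it. The article states no alpha, sidedness, design effect or dropout allowance for the calculation.

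**The concern.** With centres as the randomised unit and 75 patients in each, an ICC of 0.05 inflates the variance of the treatment comparison almost fivefold. A total of 450 is less than twice the number that an individually randomised trial would need for the same target, so the two cannot both be right. The article prints every input except alpha, so the result can be checked from the text. It is a printed figure in conflict with its neighbours, and not a detail that an article would leave to a fuller document.

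This is the article's only power statement, and it concerns the primary outcome. It tells the reader that the trial has a 10% chance of missing a true 0.5 percent difference. On the printed inputs that chance is several times larger.

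**Working it through.** **Inputs.** Difference 0.5, SD 1.2, ICC 0.05, power 90%, N = 450 (Sample Size); 6 centres of about 75 (Randomisation and Patient Recruitment); 3 intervention centres (DAFNE and Study Interventions). *Assumptions:* two-sided alpha 0.05, with one-sided 0.05 as the alternative; no dropout and equal cluster sizes, both of which favour the plan.

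**1. Trying to reproduce 450.**
- Individual randomisation: n per arm = 2 × (1.960 + 1.282)² × 1.2² / 0.5² = 121.0.
- Design effect: 1 + (75 − 1) × 0.05 = 4.7.
- Clustered: 121.0 × 4.7 = 569 per arm, about 1,138 in total. At 75 per centre this is 569 / 75 = 7.6, so 8 centres per arm.
- With a t reference on 2k − 2 df for k centres per arm, 8 per arm gives 87% and 9 per arm gives 91%, so 9 are needed.

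The figure of 450 is not reproduced. It appears only if the cluster size is about 18: the design effect is then 1 + 17 × 0.05 = 1.85, and with n rounded up to 122 per arm, 2 × 122 × 1.85 = 451. That means about 450 / 18 = 25 clusters, and the trial has 6.

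**2. Power at 6 × 75.**
- Effective n per arm: 225 / 4.7 = 47.9.
- SE of the difference: 1.2 × √(2 × 4.7 / 225) = 0.245.
- Standardised difference: 0.5 / 0.245 = 2.04.

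| Alpha | Normal approximation | t, 4 df |
|---|---|---|
| Two-sided 0.05 | 53.1% | 34.6% |
| One-sided 0.05 | 65.3% | 51.7% |

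**3. Whether more patients per centre would help.** As cluster size grows without limit, the SE falls only to 1.2 × √(2 × 0.05 / 3) = 0.219, and 0.5 / 0.219 = 2.28. Two-sided power stops at 62.6% (normal) or 41.4% (t, 4 df). Equivalently, 90% power requires more than 121.0 × 0.05 = 6.05 centres per arm, and there are 3.

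**4. Detectable difference at 90% power, two-sided 0.05.** Normal: (1.960 + 1.282) × 0.245 = 0.80. Noncentral t on 4 df: 1.08.

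**5. What would make 450 give 90% with 6 centres of 75.** Each row changes one input and holds the others as printed.

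| Input changed | Power, normal | Power, t on 4 df |
|---|---|---|
| ICC about 0.012 | 90% | below 71% (71% at ICC 0.01) |
| ICC 0 | 99% | 90% |
| SD about 0.75 | 90% | 69% |
| SD 1.0 | 69% | 46% |

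**The case against.** - **Alpha is not stated.** The exact percentages are therefore conditional. This stands, and the range is shown. It does not rescue the claim, because one-sided 0.05 still gives only 65% or 52%.
- **The SD may be the wrong one.** The article calls 1.2 the SD of HbA1c, while the primary outcome is change. A smaller SD of change would raise power, and an SD near 0.75 would restore 90% by the normal approximation. This also stands. It follows that a reader must not take 53% or 35% as the trial's actual power: they are power under the printed inputs. Nor is a smaller ICC the only route to 90%. But the article gives no other SD, and the printed one does not support the printed power.
- **The 4 df figure presupposes an analysis.** Planned Analyses does not specify a cluster-level t-test, and a small-sample correction may be left to a document not shown. That is fair. The 35% is a sensitivity figure, and the finding rests on the 53%.
- **Two further inferences are tempting, and the article does not support either.** One is that the 0.5 target must be diluted because patients with HbA1c below 7.5 percent are included. Sub-group analyses does say that benefit for individuals with low HbA1c "may amount to a reduction in the frequency of severe hypoglycaemia", but it speaks of DAFNE training and not of the follow-up comparison. No proportion below 7.5 percent and no expected effect in these patients is given. The other is that a null result will be misread as showing no benefit. The stated hypothesis is superiority, and nothing says that non-significance will be taken as equivalence.

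**Conclusion.** The power sentence is wrong as written. With SD 1.2, ICC 0.05 and 6 centres of about 75, 450 patients give about 53% power for a 0.5 percent difference (normal approximation), or about 35% on 4 df, and not 90%. The implied chance of missing that difference is about 47% to 65%, and not 10%. No cluster size repairs this with 3 centres per arm at that ICC.

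The percentages rest on an assumed two-sided alpha of 0.05, equal clusters and no dropout. That the inputs fall short of 90% also holds at one-sided 0.05. The finding concerns consistency between the printed inputs and the printed result. The article does not show which input, if any, differed in the calculation actually run.

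**What to change.** Replace the power sentence in Sample Size with:

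> With 6 centres of about 75, SD 1.2, ICC 0.05 and two-sided alpha 0.05, power for a 0.5 percent difference is about 53% (normal approximation) or 35% (t on 4 df); the difference detectable with 90% power is about 0.8 (normal) or 1.1 (t) percent.

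If the intended alpha differs, state it and recompute. If 450 came from a different SD (for example the SD of change), ICC or cluster size, print that value with its basis and show power over a range of it. For orientation, 90% by the normal approximation needs an ICC of about 0.012 or an SD of about 0.75. A cluster size of about 18 would have to be reconciled with the 6 centres of 75.

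The cost is text only, with no extra patients or centres. The downside is a less favourable stated power.

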#### Planned Analyses

Initially, descriptive analysis will be conducted to fully profile both the study centres (number of educators and doctors, years since initial training and size of DAFNE waiting list) and the participants (age, gender, years since diagnosis, baseline HbA_1c_, weight, lipid levels and socio-economic status). The main analysis, for the entire cohort, will be an intention-to-treat analysis and will compare differences between HbA_1c _at baseline and at 18 months in the 2 treatment arms, adjusting for age, gender, study centre and years since diagnosis. Changes in the rate of severe hypoglycaemia will also be examined.

In addition to this intention-to-treat analysis we will also undertake a "per protocol" analysis on those individuals who attended all of the educational sessions in the intervention arm.

Sensitivity analyses will explore whether adherence to the intervention influences the effect of the intervention on primary outcome.

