**Methods:**

Six participating centres were cluster randomised to deliver either group follow-up or a return to traditional one-to-one clinic visits. In the intervention arm group follow-up was delivered at 6 and 12 months post DAFNE training according to a curriculum developed for the study. In the control arm patients were seen individually in diabetes clinics as part of routine care. Study outcomes included HbA_1c _levels, self-reported rates of severe hypoglycaemia, body weight and measures of diabetes wellbeing and quality of life. These were measured at 6, 12 and 18 months after recruitment. Generalisability (external validity) was maximised by recruiting study participants from existing DAFNE waiting lists in each centre, by using broad inclusion criteria (including HbA_1c _values less than 13 percent with no lower limit) and by using existing clinic staff to deliver the training and follow-up. Internal validity and treatment fidelity were maximised by quality assuring the training of all DAFNE educators, by external peer review of the group follow-up sessions and by striving for full attendance at follow-up visits. Assays of HbA_1c _were undertaken in a central laboratory.

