#### Psychosocial analyses

With regard to the psychosocial measures, suitable numerical and graphical summaries (e.g. box plots, scatterplots and case profile plots) will be presented to summarise the within-subject (i.e. time) and between-subject (i.e. treatment group) factors.

Several analyses will be performed to compare the change in the psychosocial response variables across time and between groups. These will include linear mixed models initially, using baseline as a covariate and subsequently where the response variables will be expressed as changes from baseline. Different covariance structures will be compared in order to best model the correlation structure within subject.

An intention to treat analysis will be performed to compare the estimated effect of the psychosocial response variables when imputing values for all missing data to the results obtained when analysing the data while ignoring missing data.

Multiple imputations [26,27] will be performed using a Predictive Model Based Method where each missing value is replaced by 5 imputed values. The imputations will be generated via randomly drawn regression model parameters from the Bayesian posterior distribution based on the cases for which the imputation variable is observed.

An estimate of the difference in the mean response, for each of the psychosocial response variables of interest, when comparing those on the intervention to the controls, will be provided by pooling the results of each 'complete' model (i.e. with imputed values) using the Barnard-Rubin adjustment method [28]. The estimated coefficients, standard errors and p-values for the intervention to control comparison from the original and complete analyses will be reported for each of the psychosocial response variables in addition to the fraction of information about the coefficients missing due to non-response/non-attendance.

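### The primary HbA1c analysis adjusts the change score for four covariates but not for baseline HbA1c; adding it costs nothing, though the gain depends on how stable centre means are

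*Protocol article*

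**What the plan says.** Outcomes and Measurement defines the primary outcome as the HbA1c change "between baseline and the 18 month follow-up visit". Planned Analyses then specifies an intention-to-treat comparison of HbA1c at "baseline and at 18 months in the 2 treatment arms, adjusting for age, gender, study centre and years since diagnosis". The list has four items. Elsewhere in the planned analyses, baseline HbA1c serves only to describe the participants and to define the subgroups split at 7.5%.

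Table 2 schedules a central HbA1c at baseline, 6, 12 and 18 months.

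For the psychosocial scales the article takes a different route. The Psychosocial analyses section plans "linear mixed models initially, using baseline as a covariate", with change from baseline as the later model.

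**The concern.** Baseline HbA1c is likely to be the strongest available predictor of HbA1c change. Eligibility runs up to 13% with no lower limit, so the baseline spread is wide. The Sub-group analyses section itself expects benefit to take another form in people who start with a low HbA1c. The primary model nevertheless carries gender and diabetes duration but not this variable, while the secondary scales get a baseline-adjusted model first.

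Two things are at stake. The first is patient-level precision. The second is how the analysis treats a chance baseline difference, which with three centres per arm can be sizeable. A change score in effect fixes the baseline slope at 1. If patients regress towards the mean, that is too steep, and the arm that happened to start higher is credited with extra improvement.

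**Working it through.** The article gives no figure on this point, so there is none to reproduce. Its sample size of 450 concerns a separate matter and is not used below.

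**Inputs from the article.** SD of HbA1c 1.2 and ICC 0.05 (Sample Size); target "difference between the 2 arms of the study of 0.5 percent from month 6 onwards" (Sample Size); six centres of about 75 (Randomisation and Patient Recruitment), three of them in the intervention arm (DAFNE and Study Interventions).

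**Assumptions.** The correlation r between a patient's baseline and 18-month HbA1c is not given; 0.5 and 0.7 are used, with 0.3 to 0.8 as the outer range. The correlation over time of centre effects, rc, is not given either. SDs are taken as equal at both times.

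**Step 1: chance baseline difference between arms.**
Variance of a centre mean = 1.44 × (0.05 + 0.95/75) = 0.0720 + 0.01824 = 0.09024.
SD of the arm difference = √(2 × 0.09024/3) = 0.245% HbA1c.
Under individual randomisation it would be 1.2 × √(2/225) = 0.113.

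**Step 2: shift in the change-score contrast if rc = r.** Shift = (1 − r) × imbalance. For a 1-SD imbalance:
- r = 0.5: 0.5 × 0.245 = 0.12, or 25% of the 0.5 target
- r = 0.7: 0.3 × 0.245 = 0.07, or 15%
- over r = 0.8 to 0.3: 0.05 to 0.17, or 10 to 34%

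**Step 3: variance if rc = r.** Change score: 2(1 − r)s². Baseline-adjusted (ANCOVA): (1 − r²)s². Ratio = (1 + r)/2, which is 0.75 at r = 0.5 and 0.85 at r = 0.7, so 25% and 15% lower. Over r = 0.3 to 0.8 the ratio runs from 0.65 to 0.90.

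**Step 4: what if centre effects are more stable than patient values?** Between-centre variation is 0.0720/0.09024 = 80% of the variance of a centre mean, so rc matters more than r. With a patient-level slope r, the variance per centre is:
- change: 0.0720 × 2(1 − rc) + 0.01824 × 2(1 − r)
- ANCOVA: 0.0720 × (1 + r² − 2·r·rc) + 0.01824 × (1 − r²)

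Example, r = 0.5 and rc = 0.8: change = 0.0288 + 0.01824 = 0.04704; ANCOVA = 0.0324 + 0.01368 = 0.04608; ratio 0.98.

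| r | rc = r | rc = 0.8 | rc = 0.9 |
|---|---|---|---|
| 0.5 | 0.75 | 0.98 | 1.19 |
| 0.7 | 0.85 | 0.90 | 1.02 |

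The shift in step 2 changes in the same way. At r = 0.5 and rc = 0.9 the slope of arm means is (0.9 × 0.0720 + 0.5 × 0.01824)/0.09024 = 0.82. A 1-SD imbalance then moves the change score by (1 − 0.82) × 0.245 = 0.04. ANCOVA with slope 0.5 under-corrects by (0.82 − 0.5) × 0.245 = 0.08.

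**Step 5: the centre term.** With centre as a fixed factor, the intercept, arm and five centre indicators make 7 columns for 6 centres, and the rank is 6. Arm is then aliased with centre, and its effect cannot be estimated. Any rewording of the covariate list has to deal with this as well.

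**The case against.** The strongest reply is that step 3 applies patient-level formulas to a trial whose precision is mostly set at centre level. This stands. Means of 75 patients need not regress as single values do, and step 4 shows the advantage disappearing or reversing under stable centre differences. Baseline adjustment cannot be presented as a guaranteed gain.

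A reader might also infer several stronger things that the article does not support:

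- **That the analysis is unadjusted, or that imbalance goes uncorrected.** Four covariates are in the model, and a change score subtracts baseline in full. The fault is over-correction when the slope is below 1.
- **That the arm starting higher will always look better.** Over randomisation the change score is unbiased. The shift is conditional on a given imbalance.
- **That open recruitment makes baseline adjustment essential.** The article does say of the pre-course visit: "During this visit a DAFNE educator would make sure that the individual met the inclusion criteria for the study". But it also describes existing waiting lists and a similar way of filling courses in each centre, and does not say whether recruitment preceded randomisation. If the arms did recruit different patients, it is not clear that ANCOVA would be less biased than a change score.
- **That ignoring the 6- and 12-month values is an error.** The analysis matches the declared 18-month outcome. With complete data a repeated-measures model gives essentially the same 18-month contrast. Handling of missing primary data may be left to the analysis plan, and the article does not say that only complete cases are analysed.
- **That this omission explains a power shortfall.** Whether 450 patients suffice is a separate sample-size question, which a baseline covariate would not settle.

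**Conclusion.** The point holds as an improvement to an analysis that the article itself fixes. Baseline HbA1c is missing from the primary covariate list, it is available for everyone, and the article already adjusts for baseline in its psychosocial models.

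If centre means regress as patients do, a 1-SD chance imbalance of 0.245% shifts the contrast by 0.07 to 0.12 (15 to 25% of the target), and adjustment lowers the variance by 15 to 25%, for r = 0.7 to 0.5. These sizes rest on an assumed r, on equal SDs at both times, and on centre-level correlation equal to patient-level correlation. If centre differences are more stable, the variance ratio moves to about 1 or above. The case for the change therefore rests on patient-level precision, consistency within the article and nil cost. It does not rest on a promised gain in power.

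**What to change.** State the primary model as 18-month HbA1c (or change, which gives the same arm coefficient once baseline is in the model) with baseline HbA1c, age, gender and years since diagnosis as covariates. Fit centre as a random effect and not as a fixed covariate, and name a small-sample degrees-of-freedom method suited to six centres. Keep the change score without baseline adjustment as a sensitivity analysis. If the two disagree, report the observed baseline difference between arms and the stability of centre means beside them.

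Optionally, fit the model to the 6-, 12- and 18-month values with arm-by-visit terms and the 18-month contrast as primary. This helps mainly when 18-month samples are missing.

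The cost is a change of analysis wording. No new data are needed, and the estimate remains the difference between arms in HbA1c at 18 months.

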Participants in the intervention arm of the study are also seen at 6, 12 and 18 months. The 6 and 12 month visits are organised as group education sessions and build on the concepts of goal setting and action planning introduced during the original DAFNE course. A follow-up curriculum was developed to guide DAFNE educators involved in delivering these sessions and specific training in the delivery of this curriculum was given to all intervention arm DAFNE educators. Groups are encouraged to determine their own priorities and select from a range of DAFNE self-management skills review topics designed specifically for these follow-up sessions. The role of the DAFNE educator is to achieve a blend of a patient-centred and curriculum-centred approach to the session. Follow-up curriculum topics include HbA_1c _and targets, diary keeping and self-monitoring, principles of dose adjustment, carbohydrate calculation, hypoglycaemic management, exercise and physical activity, alcohol and sick day rules. An example of a typical timetable for a group follow-up session is outlined in Table 1. Where DAFNE graduates are unwilling or unable to participate in a follow-up session with their original group they are offered a follow-up session with a different DAFNE group from that centre. Every effort is made to avoid delivering follow-up on a one-to-one basis in this arm of the study. In keeping with an emphasis on quality assurance an external peer review of the delivery of one 6 month follow-up session in each of the 3 intervention arm centres will be undertaken during the study.

**Table 1 T1:** Typical timetable used during the intervention follow-up sessions

09:30	Welcome
09:40	HbA_1c _results, review of blood sugar and targets

10:10	Quiz to identify 3 areas the group would like to focus on (patient-centred approach)

10:20	Curriculum used to guide group-led discussion of identified topics

12:10	Goal setting and action planning

12:30	Close

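### The main HbA1c analysis adjusts for study centre, but centre is the randomised unit and sits wholly within one arm, so the treatment effect cannot be estimated as written

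*Protocol article*

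**What the plan says.** Under Randomisation and Patient Recruitment, the article describes "cluster randomisation with the unit of randomisation being the participating DAFNE centre". It adds that "There are 6 participating centres in this study" and expects that "each cluster would have approximately 75 participants each". Each centre delivers a single follow-up method; this was chosen to limit contamination ("By randomising centres to deliver one or other method of follow-up"). DAFNE and Study Interventions refers to "each of the 3 intervention arm centres", which leaves three control centres.

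Under Planned Analyses, the main intention-to-treat analysis compares HbA1c "at baseline and at 18 months in the 2 treatment arms", "adjusting for age, gender, study centre and years since diagnosis". Centre thus appears in the same list as three patient characteristics. No random centre effect, generalised estimating equation or cluster-level method is named for this outcome. The linear mixed models under Psychosocial analyses serve other outcomes, and the correlation they are said to model is within subject, not within centre.

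The Sample Size section uses an SD of 1.2 and an intra-class correlation of 0.05.

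**The concern.** In a trial that randomises patients within centres, adjusting for centre is routine and useful. Here centres themselves were randomised, so all the randomised information about the treatment lies in differences between centres. Adjusting for centre as a covariate removes exactly those differences.

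Two things could follow. The model may return no treatment estimate. Or the software may silently drop a redundant term and return a coefficient that looks like a treatment effect but is judged against patient-to-patient error alone. An analyst who sees the problem and simply deletes centre, putting nothing in its place, meets the second difficulty in another form: the analysis then ignores the clustering that the sample size allowed for. The result at stake is the primary outcome.

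**Working it through.** **Inputs.** Six centres, three per arm, about 75 patients each (Randomisation and Patient Recruitment; DAFNE and Study Interventions). SD 1.2 and ICC 0.05 (Sample Size). The article states no significance level; two-sided 5% is assumed. It gives the SD for HbA1c; that the SD and ICC also apply to the change in HbA1c is a second assumption.

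**1. Estimability.** With an intercept, arm and five centre indicators there are 7 columns. Arm equals the sum of the indicators of the three centres in that arm, so the rank is 6. Adding age, gender and years since diagnosis gives 10 columns of rank 9. Without the centre indicators, the intercept, arm and three patient covariates have full rank (5 of 5). This does not depend on SD, ICC or sample size.

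**2. If software drops a centre indicator and keeps arm.**
- Between-centre variance: 0.05 × 1.44 = 0.072. Within-centre variance: 0.95 × 1.44 = 1.368, or 1.368/75 = 0.01824 for a centre mean.
- With reference coding, the arm coefficient is the difference between two single centres. Its true SD is √[2 × (0.072 + 0.01824)] = 0.425. The model reports √(2 × 0.01824) = 0.191.
- False-positive rate: 2 × [1 − Φ(1.96 × 0.191/0.425)] = 0.38.
- With centre effects summing to zero within arm, the coefficient is the difference between arm averages. Both variances are divided by 3 (true SD 0.245, reported 0.110), so the ratio and the 38% are unchanged.
- Simulation under no effect (5,000 runs) gave 37.9% for the first coding and 38.8% for the second.

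**3. If centre is omitted and nothing replaces it.**
- Design effect: 1 + (75 − 1) × 0.05 = 4.7.
- False-positive rate: 2 × [1 − Φ(1.96/√4.7)] = 0.37; simulation 37.8%.

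**4. If centre is treated as the cluster.**
- Six centre means less two arm means leave 4 degrees of freedom. A t-test on the centre means rejected in 5.0% of the simulated null trials.
- A random centre effect tested against 1.96 instead of the t critical value of 2.776 would give P(|t₄| > 1.96) = 0.12.

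**5. Width of the 95% interval.** The standard error that allows for clustering is 1.2 × √(2 × 4.7/225) = 0.2453.

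| Analysis | Half-width (HbA1c, percentage points) |
|---|---|
| Centre as cluster, t on 4 df | 2.776 × 0.2453 = 0.68 |
| Centre as cluster, z | 1.96 × 0.2453 = 0.48 |
| Clustering ignored | 1.96 × 1.2 × √(2/225) = 0.22 |

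**6. Sensitivity to the ICC** (75 per centre; the SD cancels from the error rates).

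| ICC | Centre fixed, one indicator dropped | Centre omitted |
|---|---|---|
| 0.01 | 0.14 | 0.14 |
| 0.02 | 0.22 | 0.21 |
| 0.05 | 0.38 | 0.37 |

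**The case against.** The best defence is that the article never says centre is a fixed covariate. It names no model, and adjusting for centre might be shorthand for a random effect, in which case the treatment effect is estimable. The surrounding text lends this some support: the authors call the trial cluster randomised throughout, used a cluster-trial sample size calculator and cite the relevant CONSORT extensions. On this view, the choice between fixed and random effects, and the degrees-of-freedom method, are details that an article may leave to the full analysis plan.

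Part of this stands. The random-effect reading is possible, and the absence of a named degrees-of-freedom method is not in itself an error. The 12% figure and the 37% for omitting centre describe analyses the article does not specify; they show what nearby choices would cost. The 38% arises only if someone reports the leftover coefficient; software that drops arm gives no result, not a false one. The ICC may also differ for change in HbA1c, and the table above shows that the inflation is smaller at lower values.

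The main point survives. The article does state the adjustment set, and it places centre between gender and years since diagnosis, where it reads as an ordinary covariate. Nothing in the primary analysis marks it as a cluster. This is a rule that is stated and does not work, not a detail left out.

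**Conclusion.** The concern holds. As written, the primary analysis either cannot estimate the treatment effect or tests it against the wrong error. The loss of estimability follows from the nesting alone and needs no numerical assumption; it is avoided only if centre was meant as a random effect, which the article does not say.

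The size of the damage, if a coefficient is reported anyway, is a false-positive rate of about 38% in place of 5% at the article's ICC, and about 14% if the ICC were 0.01. These figures assume a two-sided 5% test, equal centres of 75, and an ICC that applies to the change in HbA1c. An honest interval has half-width 0.68 at the stated SD and ICC. That is wider than the 0.5 difference the trial is designed to detect, whereas the interval that ignores clustering (0.22) gives a false impression of precision.

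**What to change.** Remove study centre from the list of adjustment covariates and state that it enters as the clustering unit. Either of these would do:

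- A linear mixed model with arm, age, gender and years since diagnosis as fixed effects and centre as a random intercept, with Kenward-Roger or Satterthwaite degrees of freedom (about 4 for the arm effect). With so few centres the between-centre variance may be estimated as zero, so the plan should say in advance what is done then.
- A two-stage analysis: adjust HbA1c change for the patient covariates without arm or centre, average the residuals by centre, and compare the three means per arm by t-test on 4 degrees of freedom (critical value 2.776).

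The two agree closely when centres are of equal size. Because they are only approximately so, one should be named as primary. The same treatment of centre should carry over to severe hypoglycaemia, the sub-group analyses by baseline HbA1c and the per-protocol analysis.

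The cost is a change of wording. No new data or change of design is needed. Confidence intervals will be wider.
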